**Intervention**

The participants will be randomly divided into the following three groups (***Figure 2)***:

1. The NoV arm: no ventilation during CPB.
2. The LOV arm: participants will receive a low V_T_ of 3-4ml/kg of IBW with the RR of 10-12 acts/min, and the PEEP of 5-8cmH_2_O during CPB; the FiO_2_ is 30% with a flow of 2 L/min.
3. The HOV arm: participants will receive a low V_T_ of 3-4ml/kg of IBW with the RR of 10-12 acts/min, and the PEEP of 5-8cmH_2_O during CPB; the FiO_2_ is 80% with a flow of 2 L/min.

FiO_2_ 80% will be applied during oxygenation for denitrogenation 5 minutes before endotracheal intubation. The lung protective ventilation strategy [34, 37-39] will be applied in the participants before and after CPB: V_T_ =6-8ml/kg IBW, PEEP=5-8 cmH_2_O，inspiration/expiration time ratio（I:E）=1:2，RR=10-12 to maintain end-tidal carbon dioxide partial pressure (P_ET_CO_2_) between 35-45 mmHg, and the FiO_2_ is set to 50%, maintaining pulse oxygen saturation (SpO_2_) ≥95%, with a flow of 2 L/min. If the SpO_2_ cannot be maintained, the anesthesiologists firstly improve patient oxygenation by changing ventilation parameters and ventilation strategies, such as the application of lung alveolar recruitment maneuver (ARM), and then consider increasing the FiO_2_. ARM is performed in all participants at the end of CPB, with manual ventilation creating the airway pressure at 30 cmH_2_O for at least 5 seconds. Vasoactive drugs will necessarily be medicated if the hemodynamics is affected by the ARM. Maintaining mixed venous oxygen saturation (SvO_2_) ≥ 60% during the CPB (70%-80% would be preferred).

The synchronized intermittent mandatory ventilation (SIMV) mode will be applied once the participants transferred to the ICU. The ventilator parameters settings are as follow: V_T_ =6-8ml/kg of IBW, PEEP=8cmH_2_O, I: E=1:2, FiO_2_=50%. FiO_2_ is adjusted according to the PaO_2_ by performing arterial blood gas (ABG) analyses: if PaO_2_≥150mmHg, it is decreased by 10%; but if PaO_2_≤80mmHg, then it is increased by 10%; minimum FiO_2_ is 30%. Any additional ARM will be recorded. Other therapeutic approaches and decisions are up to the ICU physicians.

**Perioperative management and monitoring**

All these participants will be managed and monitored following the general standard of the practices of the Department of Anesthesiology, West China Hospital of Sichuan University no matter which group they belong to. Intraoperative standard monitoring includes capnography, electrocardiogram (ECG), pulse oximeter, invasive arterial blood pressure, central venous pressure, urine output, nasopharyngeal temperature, transesophageal echocardiogram (TEE), activated clotting time (ACT). Other managements are optional, including bispectral index (BIS) and cerebral oxygen saturation monitoring.

The anesthesiologists give the participants heparin (3 mg/kg) to obtain an ACT of 280s for aortic cannulation and 480s before starting the CPB. At the end of the CPB, protamine is given to antagonize heparin with 1:1. The target ACT is about the same as the baseline value. Mean arterial pressure will be kept between 50 and 70 mmHg during CPB.

Respiratory management, including extubation and the application of supplemental oxygen therapies, were independently carried out by the intensivists and respiratory therapists. The protocol of weaning from invasive ventilation was showed in ***Figure 3.*** The detailed extubation criteria were listed in Table 3.

**Data collection**

All the related data are collected on the CRF. Preoperative data include age, height, weight, EuroSCORE Ⅱ, smoking status, diabetes mellitus, peripheral arterial disease, pulmonary comorbidity, pulmonary infection in the past 30 days and the classification of American Society of Anesthesiologists (ASA). Intraoperative data include type and duration of surgery procedure, duration of CPB and aortic cross clamp, units of allogeneic red blood cell transfusions, volume and type of fluids administered. Postoperative data include time to extubation, need for non-invasive ventilator, re-intubation, postoperative hospital stay, temperature, leukocyte count and chest X-ray. Other data at three time points (the moment arriving in the ICU, 6 and 12 hours after arrival in the ICU) include PaO_2_, FiO_2_, and partial pressure of carbon dioxide (PaCO_2_). PPCs events are traced throughout the hospitalization.

**Statistical considerations**

**Sample size**

Sample-size calculation is based on two-sided alpha error of 0.05 and 80% power. We performed a pilot-study, showing that the P_max_ is 40% in the LOV group (15 patients) and the P_min_ is 22% in the NoV group (14 patients). Therefore, we expect a reduction of 45% in the incidence of this parameter, and then calculate the sample size of 127 patients per group (381 in total). Considering a dropout fraction of 10%, we will finally need a total of 420 participants.

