**Data analysis**

Data will be analyzed following the intention-to-treat principle using SPSS version 22.0 (SPSS, Chicago, IL, USA). Comparisons in the dichotomous variables will be made by the chi-square tests (or Fisher exact tests where numbers are small). Comparisons in the continuous variables will be made by analysis of variance or the nonparametric Kruskal-Wallis H test. Two-sided significance tests will be used throughout. The Results will be presented as n (%), mean (SD), or median (interquartile range). Bonferroni correction will be used when doing post hoc analysis.

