**Discussion**

About 1-1.25 million patients undergo cardiac surgery worldwide each year and the number continues to increase [40]. CPB is an essential part of major cardiac surgery which may induce PPCs after operation. Since the PPCs are leading causes of mortality and morbidity [37], the effective preventive measures are particularly important and urgently needed. Various researches have been performed to reach this goal. The MECANO trial (NCT03098524) aims to assess the effects of mechanical ventilation (V_T_: 3ml/kg, PEEP: 5cmH_2_O, RR: 5bpm) on all-cause mortality and respiratory failure comparing with no ventilation during CPB [41]. It does not provide the detailed usage of oxygen though the ambitious number of patients (n=1500). The CPBVENT trial (NCT02090205) is a three-armed multicenter study [42], which compares two different ventilation strategies (CPAP: 5cmH_2_O or V_T_: 2-3ml/kg of IBW, PEEP: 3-5cmH_2_O, RR: 5bpm) with no ventilation during CPB. This trial’s primary endpoint (PaO_2_/FiO_2_ ratio) can be easily identified, observed, and calculated, but indirect. That is why we use it as a secondary endpoint. Besides, the inclusion and exclusion criteria are relatively strict, making the conclusion only applicable to a specific group of populations. The purpose of the VONTCPB study is to determine the impact that the different FiO_2_ has on the PPCs when combining the ventilation strategy with low V_T_（3-4ml/kg of IBW, only about half of the normal tidal volume）, routine respiratory rate (10-12 bpm) and PEEP (5-8 cmH_2_O) during CPB. This trial is the first study to investigate the effect of oxygen under different ventilation strategy during CPB. The number of the sample size (n=420) is adequate. The primary endpoints are clinically relevant. The purpose of setting ventilator parameters in this way is to make the ventilation closer to the general. And this ventilation management during CPB may potentially benefit patients’ outcomes, but at the same time it has an imperceptible impact on the operating field.

There are limitations of the trial due to the inherent properties such as its single-center design. It is questionable whether the conclusion drawn by the VONTCPB trial can be applied in other hospitals because of the different clinical practice in other hospitals. Besides, only the volume controlled ventilation mode is applied, so it is unknown whether it is also applicable in other ventilation mode, such as pressure controlled mode.

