In general, the VONTCPB trial would answer the question that whether maintaining mechanical ventilation during CPB is more preferable than no ventilation. Better still, which level of FiO_2_ is beneficial to patients will be determined from this trial.

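### 127 per group supports a three-arm overall test; the pairwise low- versus high-FiO2 comparison is not shown to be powered, so the Discussion claims more than the calculation supports

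*Protocol*

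**What the plan says.** Protocol, Sample size: "Sample-size calculation is based on two-sided alpha error of 0.05 and 80% power". The pilot figures are given as "P_max_ is 40% in the LOV group (15 patients" and "P_min_ is 22% in the NoV group (14 patients". The section describes this as a 45% reduction (1 − 0.22/0.40 = 0.45), "and then calculate the sample size of 127 patients per group (381 in total", and then: "Considering a dropout fraction of 10%, we will finally need a total of 420 participants". It names no test or formula and gives no rate for the HOV arm.

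Protocol, Data analysis: dichotomous endpoints are compared by chi-square or Fisher tests, and "Bonferroni correction will be used when doing post hoc analysis". The number of comparisons is not given.

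Protocol, Discussion: "The number of the sample size (n=420) is adequate". The same section makes the effect of FiO2 on pulmonary complications the purpose of the study. It closes by saying the trial will answer whether ventilation is preferable to none, and that "which level of FiO_2_ is beneficial to patients will be determined from this trial".

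**The concern.** An overall three-arm test asks whether the arms differ anywhere. The Discussion promises something else: ventilation against none, and low against high FiO2. Both are pairwise contrasts, and the second is LOV against HOV, the arm whose rate is not stated. An 80% figure for the overall test does not pass to each pair, least of all after a Bonferroni correction.

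At stake is the comparison that sets this trial apart from the others the Discussion cites. If its power is low, the likely result is a non-significant LOV–HOV difference with a wide interval, and the FiO2 question stays open although the protocol says it will be settled.

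**Working it through.** **Inputs.** From Sample size: two-sided alpha 0.05, power 80%, LOV 40%, NoV 22%, 127 per group, dropout 10%, total 420. From Randomization/Blinding: 1:1:1 allocation. Assumed: HOV between 22% and 40%, because LOV is labelled the maximum and NoV the minimum; three Bonferroni pairs, alpha 0.05/3 = 0.0167.

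**Reproducing 127.** As one comparison of 40% with 22%,

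n = [z(1−α/2)·√(2p̄q̄) + z(0.80)·√(p1q1 + p2q2)]² / (p1 − p2)²,

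with p̄ = 0.31, √(2p̄q̄) = 0.654 and √(p1q1 + p2q2) = 0.642:
- alpha 0.05: 102.4, so 103 per group
- alpha 0.05/2: 125 per group
- alpha 0.05/3: 136.9, so 137 per group

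As a three-arm chi-square on 2 df, the noncentrality for 80% power is 9.635 and n = 9.635 / [Σ(p − p̄)²/(p̄q̄)]. With HOV at the midpoint, 31%, the bracket is 0.0162/0.2139 = 0.0757 and n = 127.2. The arcsine formula using only the highest and lowest rates, 2 × 9.635/(2asin√0.40 − 2asin√0.22)², gives 124.7. The three-arm reading fits best.

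**Does it depend on HOV = 31%?** Overall power at 127 per group:

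| HOV rate | 22% | 25% | 28% | 31% | 32% | 35% | 40% |
|---|---|---|---|---|---|---|---|
| Power | 92% | 87% | 82% | 80% | 80% | 82% | 89% |

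About 31–32% is the least favourable value, so 127 is close to a worst-case size.

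**LOV versus NoV.** Power = Φ{[|p1 − p2|√n − z(1−α/2)√(2p̄q̄)] / √(p1q1 + p2q2)}. At n = 127 and alpha 0.05/3: (0.18 × 11.269 − 2.394 × 0.654)/0.642 = 0.72, giving 76%. Without correction it is 88%, with two comparisons 81%, and with three comparisons at 140 per group (no dropout) 81%.

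**LOV versus HOV.** The same formula at 127 per group, LOV 40%:

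| HOV rate | alpha 0.05/3 | alpha 0.05 |
|---|---|---|
| 22% | 76% | 88% |
| 25% | 56% | 73% |
| 28% | 35% | 52% |
| 31% | 18% | 32% |
| 34% | 8% | 17% |
| 37% | 3% | 7% |

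HOV versus NoV moves the other way: at alpha 0.05/3 it is 3% at HOV 25%, 22% at 31% and 59% at 37%. No HOV rate in the range powers both HOV contrasts.

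**Precision.** With 40% against 31% at 127 per group, the 95% half-width is 1.96 × √[(0.24 + 0.2139)/127] = 0.117, about 12 percentage points either side.

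**Dropout.** 127 × 1.10 = 139.7, so 140 per group and 420 in total. But 420 × 0.90 = 378, or 126 per group, while 381/0.90 = 423.3. At 126 per group the overall power is about 79.5–80% at worst.

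**Closed procedure.** Test the three arms together at 0.05 and, only if that is significant, each pair at 0.05. With three arms, any two true pairwise nulls imply the global null, so no further step is needed for strong family-wise control. Simulation at 127 per group gives a family-wise error of about 5% under the global null and 4.9% when only two arms are equal. At 22/31/40%, compared with three-pair Bonferroni, power rises from 77% to 80% (LOV v NoV), 18% to 32% (LOV v HOV) and 22% to 36% (HOV v NoV). For any pair, the closed procedure's power cannot exceed that pair's unadjusted power at alpha 0.05.

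**The case against.** The strongest reply is that the stated number is right. It reproduces, holds at about 80% or better over the whole range that the pilot allows, and needs no hidden HOV rate. That stands. A reader might infer that 127 is a miscalculation, or that it works only if HOV is secretly set at 31%. Neither inference is supported.

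Second, the pairwise figures rest on choices the protocol does not state. Three comparisons are assumed; with two, or with all 140 per group evaluable, LOV versus NoV reaches 81%. Analysis is by intention to treat and the primary endpoints are in-hospital, so 140 is a fair upper bound. This also stands, and it is why the 76% is conditional. It does not rescue the FiO2 contrast. Even with no multiplicity correction, LOV versus HOV has at most 73% power once HOV is 25% or higher. At 140 per group with three pairs it reaches 81% only if HOV equals 22%.

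Third, it is tempting to quote 18% for LOV versus HOV and 22% for HOV versus NoV as properties of the design. They are not; they follow from an assumed 31%, and the range must be shown.

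Fourth, Bonferroni is valid, and details of multiplicity may sit in an analysis plan that is not at hand. That is so. The closed procedure is offered as a gain over the stated rule, not as the repair of an error. Nor does the protocol plan an equivalence claim, so no such claim should be attributed to it.

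**Conclusion.** The concern holds as an unsupported claim, not as an arithmetic error. The 80% belongs most plausibly to the three-arm overall test. It is not shown for the pairwise contrasts on which the Discussion's conclusions rest. At 127 per group with three Bonferroni pairs, LOV versus NoV has 76% power, and LOV versus HOV is below 80% at every HOV rate from 22% to 40%, falling to 3% at 37%. For the FiO2 question, the statements that the sample size is adequate and that the trial will determine the answer are therefore unsupported.

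These figures assume that the pilot rates are true, that HOV lies between them, that there are three comparisons, and that 127 per group are evaluable. The pilot arms had 15 and 14 patients, so the rates themselves are uncertain. The mismatch between 378 and 381 is real but minor.

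This should be fixed; it does not undermine the trial's overall test.

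**What to change.** 1. **Sample size.** State which test the 80% refers to. The sponsor should give its own HOV rate or, failing that, show pairwise power across 22% to 40%; 31% should not be written in as if it had been the sponsor's assumption. Say how many pairwise comparisons are intended. Restate the evaluable number after 10% dropout as 378 (126 per group).
2. **Discussion.** Replace the claims of adequacy and of determining the better FiO2 with a commitment to estimate the LOV minus HOV difference in the composite endpoint with a confidence interval, and say that this contrast has limited power.
3. **Data analysis.** For the composite pulmonary complication endpoint, replace Bonferroni by the closed three-arm procedure: overall chi-square at 0.05, then each pair at 0.05 only if the overall test is significant.

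The cost is text in three sections and no additional patients. The stated pairwise power will look less favourable than the current wording suggests. Step 3 raises pairwise power at no cost in family-wise error, but LOV versus HOV remains underpowered for most HOV rates, so step 2 is needed either way. For scale, 80% power for 40% against 31% at alpha 0.05/3 would take 591 per group, which is why estimation is the realistic aim.

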**Data analysis**

Data will be analyzed following the intention-to-treat principle using SPSS version 22.0 (SPSS, Chicago, IL, USA). Comparisons in the dichotomous variables will be made by the chi-square tests (or Fisher exact tests where numbers are small). Comparisons in the continuous variables will be made by analysis of variance or the nonparametric Kruskal-Wallis H test. Two-sided significance tests will be used throughout. The Results will be presented as n (%), mean (SD), or median (interquartile range). Bonferroni correction will be used when doing post hoc analysis.

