**Endpoints**

The primary endpoints are the incidence of a composite of PPCs and the PPCs score during hospital stay [35-37]. The detailed definitions of PPCs are shown in ***Table 1***. The score is presented in ***Table 2***. Secondary endpoints are listed as follows: the incidence of oxygen index <300 mmHg at three time points (the moment arriving in the ICU, 6 and 12 hours after arrival in the ICU), the surgical incision healing grade, the intubation time, the length of ICU stay and hospital stay, and postoperative 30-day mortality rate.

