**Randomization/Blinding**

The random number table was generated by Microsoft Excel in a 1:1:1 treatment ratio. The investigator who is responsible for grouping visits the patients the day before surgery and gets the consents. Once the patient is qualified, he determines the serial number and random number of the patient and writes on the Case Report Form (CRF). He will also inform the anesthesia care providers who do not participate in the study the treatment of the patient. The patient, the data collector and the intensivist are not aware of the treatment information in the whole process. Any intraoperative event (such as pleura incision) or deviation from the protocol is recorded on the CRF.

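### Both primary endpoints are set for unadjusted tests although likely prognostic preoperative covariates are collected; a prespecified adjusted analysis would be a modest, nearly free gain in efficiency

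*Protocol*

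**What the plan says.** The protocol's Data analysis section assigns tests by type of variable. For binary outcomes: "Comparisons in the dichotomous variables will be made by the chi-square tests (or Fisher exact tests where numbers are small". For continuous outcomes it names analysis of variance or Kruskal-Wallis. No regression model or covariate appears in that section.

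The Endpoints section names two primary endpoints, the incidence of composite PPCs and the PPCs score. The first is binary and goes to the chi-square. The second is a graded score (Table 2) that the section does not mention by name; by default it goes to analysis of variance or Kruskal-Wallis. Both are unadjusted.

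The Data collection section lists preoperative items recorded for each patient. Besides age and EuroSCORE II they include "smoking status, diabetes mellitus, peripheral arterial disease, pulmonary comorbidity, pulmonary infection in the past 30 days".

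On allocation, the Randomization/Blinding section says "The random number table was generated by Microsoft Excel in a 1:1:1 treatment ratio". It mentions neither blocks nor strata.

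**The concern.** Eligibility is broad: adults having elective cardiac surgery through a median sternotomy on bypass, with a short list of exclusions. Baseline risk of a pulmonary complication is likely to vary across such patients, and several of the recorded preoperative items plausibly predict it. An unadjusted test leaves that predictable variation unused. If the items are prognostic, a model containing them has more power from the same patients, and the estimated arm difference takes account of any chance difference in case mix.

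The choice has to be made in advance. If the arms turn out to differ on, say, pulmonary comorbidity, an adjusted result chosen after seeing the data would look selective. The trial also has little spare power: it is sized at 80% for the overall three-arm comparison, while the closing discussion promises answers to pairwise questions (ventilation against none, and which oxygen level), and post hoc comparisons carry a Bonferroni correction.

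**Working it through.** **Inputs from the Sample size section.** "Sample-size calculation is based on two-sided alpha error of 0.05 and 80% power"; "the P_max_ is 40% in the LOV group (15 patients"; "the P_min_ is 22% in the NoV group (14 patients"; "we expect a reduction of 45% in the incidence of this parameter" (check: (0.40 − 0.22)/0.40 = 0.45). Stated result: 127 per group, 381 in total, 420 after a 10% dropout allowance.

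**Assumption.** The protocol gives no rate for the third arm. I put it at the midpoint, 0.31.

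**Step 1: reproduce 127 per group.** For a three-group chi-square with 2 degrees of freedom at alpha 0.05 and 80% power, the required noncentrality is λ = 9.635.

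- Mean rate: (0.22 + 0.31 + 0.40)/3 = 0.31.
- Noncentrality per patient per arm: Σ(pᵢ − 0.31)² / [0.31 × 0.69] = (0.0081 + 0 + 0.0081)/0.2139 = 0.07574.
- n per arm = 9.635/0.07574 = 127.2, against 127 stated.

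The arcsine formula on the highest and lowest rates, n = 2λ/d² with d = 2·arcsin√0.40 − 2·arcsin√0.22, gives 124.7. An ordinary two-arm calculation gives 103 (114 with continuity correction), so it is not the basis. The planned test and the sample size agree: at 127 per arm the noncentrality is 127 × 0.07574 = 9.62 and power is 79.9%.

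**Step 2: what adjustment could add.** The protocol gives no prognostic strength for any covariate, so this is an assumed range. In the simulation there were 4,000 trials per setting, 127 per arm, rates 0.22/0.31/0.40, and one normally distributed baseline risk score. The comparison was the unadjusted chi-square against the 2-df likelihood-ratio test for arm in a logistic model containing the score.

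| Odds ratio per SD of score | AUC | Power, unadjusted | Power, adjusted | Gain (points) |
|---|---|---|---|---|
| 1.0 | 0.50 | 82.5% | 82.8% | 0.3 |
| 1.5 | 0.61 | 80.6% | 82.7% | 2.1 |
| 2.0 | 0.68 | 80.2% | 84.0% | 3.8 |
| 3.0 | 0.75 | 80.9% | 87.9% | 7.0 |

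The simulation standard error of each power is about √(0.8 × 0.2/4000) = 0.6 points. The arm rates are the same in every row, so differences down the unadjusted column are simulation noise; the within-row gain is the figure to read.

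**Step 3: type I error.** With all three rates at 0.31, rejection rates were 4.6% to 5.4% unadjusted and 4.7% to 5.3% adjusted. Both methods hold the 5% level.

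**The case against.** The strongest reply is that nothing here is wrong. The chi-square is valid under randomisation, holds its level, and is the test on which the sample size rests. The gain depends on covariate strength that the protocol does not give, and it is zero if the covariates are not prognostic. Adjusted models are also often left to a statistical analysis plan, which is not shown. Most of this stands, and it sets the weight of the point. It does not remove it: the protocol has already named the tests, and an adjusted analysis is a better use of data it already collects.

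A reader might infer more than the protocol supports.

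- *That the unadjusted test gives away balance or biases the result.* Balance comes from randomisation, not from the test. Chance imbalance is already allowed for in the test's error rate, and adjustment corrects for imbalance without creating balance.
- *That allocation is known to be unstratified.* The protocol is silent on strata and blocks, which is not the same.
- *That adjustment makes the 420 patients act like 467 to 525 and lifts power from 80% to 84–88%.* The first range is 420/0.90 to 420/0.80, with 10% to 20% explained variance assumed. But 80% power belongs to 127 per arm. At 140 per arm, which is the 420 before any dropout, the unadjusted test already has 83.9% (noncentrality 140 × 0.07574 = 10.60).
- *That the oxygenation endpoint,* "the incidence of oxygen index <300 mmHg at three time points"*, shows the same fault.* That is a separate trade-off on a secondary endpoint: a ratio below 300 is a respiratory-failure criterion in Table 1, and a single model over three times would not settle multiplicity unless one contrast were named.

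**Conclusion.** The point holds as a recommended improvement and not as a defect. The protocol fixes unadjusted tests for both primary endpoints while collecting likely prognostic preoperative covariates and describing no stratification. The planned chi-square is sound and delivers about the planned 80% power at 127 per arm.

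For composite PPCs, adjustment at the same size would add nothing if the covariates do not predict the outcome, about 2 to 4 points if they predict it moderately (AUC 0.61 to 0.68), and about 7 points if they predict it strongly (AUC 0.75). These figures rest on the assumed middle-arm rate of 31%, on the assumed range of prognostic strength, and on a single well-specified risk score. No gain was computed for the PPCs score.

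**What to change.** In the Data analysis section:

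1. Name as the primary analysis of composite PPCs a logistic model with arm and a short fixed list of preoperative covariates, for example EuroSCORE II, age, pulmonary comorbidity, smoking and lung infection in the past 30 days.
2. Exclude anything measured after randomisation, such as bypass or cross-clamp duration.
3. Report standardised risk differences between arms with 95% confidence intervals.
4. Keep the chi-square as a supportive analysis.
5. Analyse the PPCs score with the same covariates, for example in a proportional-odds model.

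In the Randomization/Blinding section, state whether allocation is blocked or stratified; if it is stratified, the stratification factors belong in the model.

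The cost is wording plus a little extra analysis work. The models run in the SPSS already named; the standardised risk differences and their intervals need a short additional step. No new data or patients are needed.

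### With exactly three arms, Bonferroni on the pairwise comparisons of the primary incidence gives up power that error control does not require

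*Protocol*

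**What the plan says.** The Objectives section sets a comparison of three strategies (NoV, LOV, HOV) on the incidence of PPCs. The Data analysis section assigns chi-square or Fisher tests to binary variables and adds that "Bonferroni correction will be used when doing post hoc analysis". It does not state how many comparisons are corrected, or whether they follow only after a significant three-arm test.

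The Sample size section states: "Sample-size calculation is based on two-sided alpha error of 0.05 and 80% power". It takes the highest and lowest pilot rates, 40% (LOV) and 22% (NoV), and arrives at 127 per arm, 381 in all, raised to 420 for dropout. It gives no HOV rate.

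The closing paragraph of the Discussion says the trial "would answer the question that whether maintaining mechanical ventilation during CPB is more preferable than no ventilation", and then that it will determine which FiO2 level benefits patients. Earlier in the Discussion, the aim is put as: "The purpose of the VONTCPB study is to determine the impact that the different FiO_2_ has on the PPCs".

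**The concern.** A significant three-arm test says only that the three rates are not all equal. Whether ventilation differs from none, and whether 80% oxygen differs from 30%, can be read only from LOV v NoV, HOV v NoV and HOV v LOV. The clinical conclusions therefore rest on the comparisons to which the Bonferroni correction applies.

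For three arms that correction is stricter than it has to be. If the pairs are tested only after a significant three-arm test, each can be tested at 0.05 without raising the family-wise error above 0.05. At 0.0167 a real difference between two arms is more likely to be missed, with no error control needed in return.

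**Working it through.** **Inputs.** From the protocol: two-sided alpha 0.05, power 80%, 127 per arm, 1:1:1 allocation, rates 40% and 22%. Assumed: the HOV rate, taken from 22% to 40%, and Bonferroni over all three pairs, 0.05/3 = 0.0167.

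**The plan's own figure.** A three-arm chi-square test (2 df) at 0.05 with 80% power needs a noncentrality of 9.635. With rates 40%, 31% (assumed middle arm) and 22%, the mean is 31%, and the effect per patient in each arm is (0.09² + 0 + 0.09²)/(0.31 × 0.69) = 0.0162/0.2139 = 0.0757. Then 9.635/0.0757 = 127.2, which matches 127. A single pair at 0.05 gives 103, and a pair at 0.0167 gives 137. The stated size thus fits a three-arm first test. Dropout: 381 × 1.1 = 419.1, so 420.

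**One pair by formula.** Power = Φ{[Δ√n − z√(2p̄(1−p̄))]/√(p₁q₁ + p₂q₂)}, where q = 1 − p, with Δ = 0.18, n = 127, p̄ = 0.31.
- Δ√n = 0.18 × 11.269 = 2.028; √(2 × 0.31 × 0.69) = 0.654; √(0.24 + 0.1716) = 0.6416.
- At 0.0167, z = 2.394: (2.028 − 1.566)/0.6416 = 0.72, power 76.5%.
- At 0.05, z = 1.960: (2.028 − 1.282)/0.6416 = 1.16, power 87.8% before the three-arm test is required as well.

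**Why 0.05 per pair is enough.** There are three pairwise null hypotheses. If any two are true, all three rates are equal. The closed family therefore holds only the three-arm null and the three pairs.
- All rates equal: a false claim needs a significant three-arm test, which happens at most 5% of the time.
- Exactly one pair equal: only that pair can be falsely rejected, at most 5% of the time.
- No pair equal: no false rejection is possible.

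**Simulation.** 400,000 trials per setting, 127 per arm, Pearson chi-square without continuity correction. Bonferroni figures are for pairs tested after a significant three-arm test; in the settings with a true difference, dropping that condition changes them by less than one percentage point.

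| True rates NoV/LOV/HOV | Comparison | Bonferroni 0.0167 | Three-arm test, then 0.05 |
|---|---|---|---|
| 31/31/31 | any false claim | 0.042 (0.045 without the three-arm test) | 0.050 |
| 40/22/22 | each true difference | 77% | 86% |
| 40/22/22 | true-null pair rejected | 1.6% | 4.9% |
| 22/40/22 | LOV v NoV | 77% | 86% |
| 22/40/31 | LOV v NoV | 76% | 80% |
| 22/40/31 | HOV v NoV | 22% | 36% |
| 22/40/31 | HOV v LOV | 18% | 32% |
| 22/40/40 | LOV v NoV | 77% | 85% |

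The 40/22/22 row reverses the pilot direction, and 22/40/22 keeps it. The figures agree because only the pattern of one arm against two matters.

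A pair significant at 0.0167 without a significant three-arm test, the only case in which the new rule loses a claim, arose in under 1% of trials in every setting.

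**The case against.** The strongest reply is that Bonferroni is valid, familiar and conservative, so preferring a closed test is a matter of taste. The protocol also never says that the three-arm test must come first. Without that gate correction is needed: uncorrected pairs have a family-wise error of about 0.123 under equal rates of 31%. Both statements are right. Nothing here says the written rule inflates error, and the gain comes from replacing one valid procedure with another. But the gate costs almost nothing, as the under-1% figure shows, and the replacement keeps the error at 0.05 while finding more true differences.

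The size of the gain also depends on the unstated HOV rate: about 9 points when HOV equals one of the other arms, and about 3 points for LOV v NoV when HOV lies midway. If all 140 randomised per arm are analysed, a 40% v 22% pair at 0.0167 has 81% power, so the loss does not always bring a pair below 80%.

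A reader might infer more: that the protocol names three conflicting deciding contrasts, or that one data set could yield opposite answers on ventilation. The documents do not support this. The Sample size section reports the extremes of the pilot rates and fits a three-arm test. The Objectives set a three-arm comparison. The two Discussion statements are compatible, as the closing paragraph lists both questions. Significant results in opposite directions would need LOV and HOV to lie on opposite sides of NoV, which nothing in the protocol suggests. A rule for split results may also stand in an analysis plan that is not shown.

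**Conclusion.** The point holds as one of efficiency. For the primary incidence, Bonferroni over three pairs costs up to about 9 percentage points of power for each true 40% v 22% difference (77% against 86%), and the closed procedure keeps family-wise error at 0.050. This rests on 127 evaluable patients per arm, the protocol's own rates, an assumed HOV rate and Bonferroni over three pairs.

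It is not a finding of invalid error control or of a wrong sample size. Nor does it call for a contrast pooling both ventilated arms against NoV. Under a Holm rule with HOV v LOV, that contrast does well when both arms share the same effect (92% at NoV/LOV/HOV 40/22/22). But it declares a ventilation effect in 44% of trials at 22/40/22, where HOV equals NoV, and at 22/40/31 it reaches 71%, less than the 76–77% of the existing LOV v NoV pair.

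**What to change.** In the Data analysis section, for the primary incidence, replace the Bonferroni sentence with wording such as:

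> The three-arm chi-square test is done first at two-sided 0.05. Only if it is significant are LOV v NoV, HOV v NoV and HOV v LOV each tested at two-sided 0.05. Conclusions on ventilation rest on the two comparisons with NoV, each reported by arm. The conclusion on FiO2 rests on HOV v LOV.

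This should replace the Bonferroni rule for that endpoint and should not be run beside a second family of contrasts. Adding a pooled contrast and HOV v LOV under Holm to this procedure raises family-wise error to 0.061 when all rates are 31%.

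The cost is wording only, with no added patients or data. There are three small downsides. No pair may be claimed if the three-arm test is not significant. The unadjusted pairwise confidence intervals are not simultaneous. The control covers one endpoint only, so it does not extend across the two primary endpoints (incidence and PPCs score).
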